# Azathioprine immunosuppression and disease modification in Parkinson’s disease (AZA-PD): a randomised double-blind placebo-controlled phase II trial protocol

**DOI:** 10.1136/bmjopen-2020-040527

**Published:** 2020-11-23

**Keywords:** Parkinson's disease, therapeutics, immunology

## Abstract

**Introduction:**

The immune system is implicated in the aetiology and progression of Parkinson’s disease (PD). Inflammation and immune activation occur both in the brain and in the periphery, and a proinflammatory cytokine profile is associated with more rapid clinical progression. Furthermore, the risk of developing PD is related to genetic variation in immune-related genes and reduced by the use of immunosuppressant medication. We are therefore conducting a ‘proof of concept’ trial of azathioprine, an immunosuppressant medication, to investigate whether suppressing the peripheral immune system has a disease-modifying effect in PD.

**Methods and analysis:**

AZA-PD is a phase II randomised placebo-controlled double-blind trial in early PD. Sixty participants, with clinical markers indicating an elevated risk of disease progression and no inflammatory or immune comorbidity, will be treated (azathioprine:placebo, 1:1) for 12 months, with a further 6-month follow-up. The primary outcome is the change in the Movement Disorder Society-Unified Parkinson’s Disease Rating Scale gait/axial score in the OFF state over the 12-month treatment period. Exploratory outcomes include additional measures of motor and cognitive function, non-motor symptoms and quality of life. In addition, peripheral and central immune markers will be investigated through analysis of blood, cerebrospinal fluid and PK-11195 positron emission tomography imaging.

**Ethics and dissemination:**

The study was approved by the London-Westminster research ethics committee (reference 19/LO/1705) and has been accepted by the Medicines and Healthcare products Regulatory Agency (MHRA) for a clinical trials authorisation (reference CTA 12854/0248/001–0001). In addition, approval has been granted from the Administration of Radioactive Substances Advisory Committee. The results of this trial will be disseminated through publication in scientific journals and presentation at national and international conferences, and a lay summary will be available on our website.

**Trial registration numbers:**

ISRCTN14616801 and EudraCT- 2018-003089-14.

Strengths and limitations of this studyFirst clinical trial of a peripherally acting immunosuppressive drug in Parkinson’s disease (PD).Robust, randomised double-blind placebo-controlled design.Novel patient stratification approach with recruitment of a more rapidly progressing subgroup to optimise chance of demonstrating clinical effect.Detailed exploratory measures examining peripheral and central immune profile in PD to demonstrate proof of mechanism.As a single centre ‘proof of concept’ trial, sample size is limited to 60 participants.

## Introduction

Parkinson’s disease (PD) is a common neurodegenerative disorder diagnosed clinically by key motor features. The core pathology in PD involves the loss of dopaminergic neurons in the substantia nigra (SN) with intracellular accumulation of alpha-synuclein aggregates (Lewy bodies). Dopamine replacement therapy can control some of the motor symptoms. However, other problems including impaired balance and cognitive dysfunction are due to more widespread neurodegenerative pathology and are consequently unresponsive to dopaminergic therapies. These symptoms progress such that by 10 years from diagnosis, around two-thirds of patients have balance and walking difficulties, and around half have dementia,^1^ with a profound impact on quality of life^2 3^ and care requirements.^4^ There are currently no treatments to alter disease course and prevent these devastating complications, hence there is an urgent need to find effective disease-modifying therapies for PD. There is increasing evidence that the immune system plays an important role in driving neurodegeneration in PD, and we propose that targeting the immune system may be an effective strategy for slowing disease progression.

The link between genetic variation in immune pathways and risk of PD is well established. Risk of developing PD is associated with polymorphisms in the human leucocyte antigen (HLA) region, which encodes proteins vital to antigen recognition and presentation.^5 6^ Large-scale analyses of Genome Wide Association Study data also implicate the immune system in PD, demonstrating heritability enrichment for genes of the adaptive immune system, including those involved in lymphocyte regulation and cytokine signalling pathways.^7 8^ Further evidence of an immune contribution to PD risk comes from epidemiological studies: individuals who regularly take non-steroidal anti-inflammatory drugs have reduced risk of developing PD,^9 10^ as do those on immunosuppressive therapy.^11^ There is also evidence that immune activation impacts on disease progression rate. In a large incident PD cohort, a proinflammatory serum cytokine profile at baseline was associated with faster motor progression and impaired cognition over 36 months of follow-up.^12^

Activation of microglia, the inflammatory cells of the brain, has been clearly demonstrated in patients with PD both at postmortem^13–16^ and using [^11^C]-PK11195 positron emission tomography (PET) imaging in vivo.^17–19^ These cells have a role in responding to tissue injury, regulating the cerebral microenvironment and antigen presentation.^20^ It is thought that this activation is driven by toxic misfolded or post-translationally modified forms of alpha-synuclein released by degenerating cells, leading to secretion of proinflammatory and neurotoxic molecules, resulting in a cyclical process of cell damage.^21^

Abnormalities in the peripheral immune profile in PD are also well demonstrated and include alterations in both the innate and adaptive immune compartments. There is a shift towards ‘classical’ (inflammatory) monocytes with elevated expression of activation markers,^22^ particularly in patients at higher dementia risk.^23^ In the T lymphocyte compartment, several authors have reported bias towards proinflammatory CD4+ lymphocyte subsets and production of proinflammatory cytokines.^24–27^ There may also be a reduction in the number and function of CD4+ T-regulatory (Treg) cells, whose role is to counter this proinflammatory response.^24 26^ In addition, changes in the CD8 compartment have been reported, with increased expression of activation markers and reduced markers of age-related senescence.^28^

Importantly, T cells with specificity for epitopes of alpha-synuclein have been identified and reported to occur at higher frequency in PD than controls; furthermore, their frequency was closely associated with possession of known PD risk alleles at the HLA locus,^29^ thus suggesting that alpha-synuclein may drive a peripheral adaptive immune response as well as an innate response of microglia in the brain. Elevated levels of alpha-synuclein specific antibodies are also present in the early stages of PD.^30^ Peripheral immune cells may contribute to brain inflammation and neurotoxicity by trafficking into the central nervous system in PD. CD4+ and CD8+ lymphocytes have been shown to be present in increased numbers in the SN at postmortem in patients with PD,^16 25^ as well as in ex vivo cerebrospinal fluid (CSF) samples.^31^ The precise mechanism by which peripheral immune cells drive neuronal damage in PD is still unclear, but it has recently been demonstrated that Th17 cells from patients with PD drive cell death in autologous induced pluripotent stem cell (iPSC) derived dopaminergic midbrain neurons.^25^

Immune manipulation in animal models of PD alters disease susceptibility and severity. Using an 1-methyl-4-phenyl-1,2,3,6-tetrahydropyridine (MPTP) mouse model of PD, studies have demonstrated that a lack of CD4+ lymphocytes attenuates dopaminergic cell death,^16^ as does administration of Treg cells.^32^ In mice that overexpress alpha-synuclein, knockout of major histocompatability class II (MHC) class II prevents both microglial activation and dopaminergic neurodegeneration.^33^ Furthermore, ciclosporin, a widely used immunosuppressant, is effective in improving motor and cognitive deficits in multiple mouse models of PD.^34^

Although animal models of PD indicate that immunomodulatory therapies may have efficacy in protecting against neurodegeneration, there is limited clinical trial data in PD to date. Phase II trials of minocycline and pioglitazone, agents that reduce microglial activation in the brain in animal models, have been negative.^35–37^ An early phase trial of sargramostim, a human recombinant granulocyte-macrophage colony-stimulating factor that promotes differentiation of proinflammatory T-effector cells into Treg cells has reported a modest improvement in an exploratory outcome of motor function over 8-week treatment.^38^

We propose that direct suppression of the peripheral immune system is an alternative, highly relevant therapeutic strategy that has not been tested in clinical trials to date. Azathioprine is an immunosuppressant drug widely used in clinical practice for a range of immune-related conditions. It is a purine analogue that inhibits nucleic acid synthesis, hence reducing proliferation of lymphocytes involved in targeting and amplification of the immune response. It affects both the cell-mediated and antibody-mediated responses through reducing T and B lymphocyte proliferation.^39^ It was selected over other immunosuppressants because of its established efficacy in a range of clinical conditions, including central nervous system disorders such as multiple sclerosis,^40^ and its acceptable safety profile with recognised protocols for toxicity monitoring. Furthermore, it is generally well tolerated in the elderly and is a once-daily preparation for ease of administration.

## Methods and analysis

### Overview

AZA-PD is a randomised, double-blind, placebo-controlled trial of azathioprine in early PD that aims to provide ‘proof of concept’ that a peripherally acting immunosuppressive drug can slow clinical disease progression. The trial will investigate whether the drug has an effect on disease course over 12 months of treatment and whether this is maintained over 6 months of subsequent follow-up. Sixty participants will be recruited and randomised 1:1 to receive active treatment or placebo. Clinical assessments will be performed at baseline, 6 months, 12 months and 18 months (6 months postcompletion of treatment), with rigorous safety monitoring. In addition, the trial aims to demonstrate ‘proof of mechanism’ by evaluating the impact of azathioprine on blood, CSF and neuroimaging parameters of immune activation in the trial population and determining the relationship between these parameters and clinical measures of disease progression.

The trial timeline is summarised in figure 1.

**Figure 1 F1:**
[figure not shown]
Overview of trial timeline. CSF, cerebrospinal fluid; PET, positron emission tomography.

Although AZA-PD is open to recruitment, given the current COVID-19 pandemic, recruitment has not commenced due to safety concerns. The Trial Steering Committee (TSC) and Data and Safety Monitoring Board (DSMB) will decide on an appropriate date to begin recruitment in due course, and protocol amendments to maximise patient safety will be submitted to the appropriate bodies when the best course of action has been determined. Our current aim is to start recruitment in March 2021, closing to recruitment in March 2022, with last patient last visit in November 2023, although this may be subject to change depending on the COVID-19 pandemic.

### Patient and public involvement (PPI)

Patients with PD and their partners and carers who attend our research clinic at the John van Geest Centre for Brain Repair (VGB), University of Cambridge, gave input into the protocol design. A PPI advisory panel of four patients/carers reviewed the protocol and provided specific feedback, leading to the addition of optional components. The PPI panel also reviewed our participant information sheet for clarity.

### Participant identification

Participants will be recruited from a single site in Cambridge, UK. Potential participants will be identified from the PD Research clinic database at the VGB. These individuals have undergone detailed clinical phenotyping, and information on demographics, comorbidities and medication is available. They have consented to be contacted about other research studies. Potential participants will be preselected by cross-referencing existing data with the inclusion/exclusion criteria outlined in figure 2. A key component of this process involves the calculation of a prognostic risk score, based on a model we have previously developed and validated, using age, Movement Disorder Society-Unified Parkinson’s Disease Rating Scale (MDS-UPDRS) axial score and semantic fluency to estimate risk of a poor prognosis (dementia, postural instability or death) within 5 years.^41^ Only patients with a risk greater than 50%, based on prior assessment at the research clinic, will be invited to take part. Approximately 40% of those on the database fall within this group. This strategy has been adopted to maximise the probability of demonstrating significant slowing of clinical progression with azathioprine treatment.

**Figure 2 F2:**
[figure not shown]
AZA-PD eligibility criteria. MDS, Movement Disorder Society; NSAIDs, non-steroidal anti-inflammatory drugs; PD, Parkinson’s disease; UKPDS, United Kingdom Parkinson's disease society; ALT, alanine transaminase; TPMT, thiopurine methyltransferase; VZV, varicella zoster virus; EBV, Epstein-Barr virus

Potential participants will be sent a copy of the participant information sheet and telephoned after 2 weeks to determine whether they are interested in participating. If so, they will attend a screening visit, where written informed consent will be obtained before confirming eligibility.

### Eligibility criteria

A potential participant will be deemed eligible for recruitment into AZA-PD if they meet the inclusion and exclusion criteria listed in figure 2. A review of medical history and blood tests will be used to determine eligibility.

### Outcome measures

The primary outcome measure is change in MDS-UPDRS gait/axial score in the OFF state over the 12-month treatment period. This is a clinical measure that has been shown to be the most sensitive measure of motor progression in PD, is relatively resistant to dopaminergic therapy and has an important impact on quality of life.^42^ This score is a sum of the points from the following sections of MDS-UPDRS part III:

3.1 – speech.3.2 – facial expression.3.9 – rising from a chair.3.10 – gait.3.12 – postural stability.3.13 – posture.3.14 – body bradykinesia.

Other outcome measures are exploratory and include:

Change in MDS-UPDRS gait/axial score in OFF state at 18 months.Change in total MDS-UPDRS in OFF state at 12 and 18 months.Change in electromagnetic sensor (EMS) measurements while performing MDS-UPDRS tremor and bradykinesia assessments at 12 and 18 months.Proportion of patients developing postural instability (Hoehn and Yahr stage 3 or greater) at 12 and 18 months.Change in global cognition (Addenbrooke’s Cognitive Examination-III (ACE-III))) at 12 and 18 months.Change in patient-reported outcome measure of quality of life (Parkinson’s Disease Questionnaire 39 (PDQ-39)) at 12 and 18 months.Change in Non-Motor Symptom Scale (NMSS) at 12 and 18 months.Change in dose of symptomatic dopaminergic therapy (Levodopa Equivalent Daily Dose (LEDD)) at 12 and 18 months.The safety and tolerability of azathioprine assessed by the number of adverse events (AEs) recorded during the 12-month treatment period.Change in [^11^C]-PK11195 PET non-dissociable binding potential (BP_ND_) in subcortical and cortical regions of interest at 12 months.Change in total lymphocyte count at 6, 12 and 18 months.Change in serum immunoglobulin levels at 6, 12 and 18 months.Change in levels of serum and CSF cytokine levels at 12 and 18 months.Change in lymphocyte subsets in blood and CSF at 12 and 18 months.

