### Trial procedures

#### Clinical

Clinical measures assessing both motor and non-motor components of PD will be performed at baseline, midtreatment, end of treatment and after 6-month further follow-up (see table 1). Throughout the course of the trial, participants will continue to take their PD medication as prescribed by their treating physician, and dose adjustments are permitted. However, some assessments will be conducted ‘OFF’ medication.

**Table 1 T1:** Schedule of assessments

	Screening visit	Imaging visit	CSF collection	Baseline visit	Monitoring visits*	Dose escalation visit	Midtreatment visit	End-of-treatment visit	Imaging visit	Follow-up visit
	Day −42 (max)	Approx. day −14±	Approx. day −7±	Day 0±14	Day 14±5 and onwards	Day 28±5	Day 182±14	Day 365±14	Day 410±45	Day 547±14
Informed written consent	✓									
Eligibility review	✓									
Randomisation				✓						
Vital signs				✓	✓	✓	✓	✓		✓
Weight in kg	✓			✓	✓	✓	✓			
Clinical assessments										
Demographics				✓						
Medical history	✓			✓	✓	✓	✓	✓		✓
Concomitant medication review	✓			✓	✓	✓	✓	✓		✓
MDS-UPDRS				✓			✓	✓		✓
NART				✓						
ACE-III				✓			✓	✓		✓
GDS				✓			✓	✓		✓
NMSS				✓			✓	✓		✓
PDQ-39				✓			✓	✓		✓
Adverse events review	✓	✓	✓	✓	✓	✓	✓	✓	✓	✓
IMP compliance check					✓	✓	✓	✓		
Imaging – optional										
(11C)-PK11195 PET-MRI		✓							✓	
Blood tests										
Screening bloods†	✓									
Safety monitoring bloods‡					✓	✓	✓	✓		✓
CRP, immunoglobulins and serum storage for cytokine measurement			✓				✓	✓		✓
Immunophenotyping			✓					✓		✓
CSF – optional										
Immune markers and immunophenotyping			✓					✓		

*Monitoring visits will take place at: day 14, day 42, day 56, day 70, day 98, day 252 and day 547 (as part of the routine follow-up visit). Additional monitoring visits may also be scheduled if there are patient safety concerns.

†Screening bloods include FBC, U&Es, LFTs, coagulation, TPMT, HIV, syphilis, hepB, hepC, EBV serology, VZV serology, LH and FSH (if female and reproductive age).

‡Monitoring bloods include FBC, U&Es and LFTs.

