#### PK-11195 PET imaging

[^11^C]-PK11195 PET will be used to measure activated microglia in the brain.^17 18^ Scanning will be conducted at the Wolfson Brain Imaging Centre (WBIC) on a GE SIGNA PET/MRI scanner, with the radiotracer produced at the WBIC Radiopharmaceutical Chemistry laboratory. MRI will be used for colocalisation. Five hundred megabecquerel of the[^11^C]-PK11195 radiotracer will be injected via a peripheral venous cannula over 30 s, and PET emission data will be acquired for 75 min postinjection in 55 time frames. Following image reconstruction and attenuation correction, specific tracer binding will be analysed with the simplified reference tissue model^51^ to quantify binding potential relative to a non-displaceable compartment (BP_ND_). The reference region will be estimated with supervised cluster analysis for [^11^C]PK11195 from existing scans in healthy controls acquired on the same scanner. BPND will be compared pretreatment and post-treatment using a region of interest approach.

Given that some participants may have difficulty tolerating prolonged PET imaging, this will be optional. It will be performed between screening and baseline and repeated within 3 months following the end of treatment.

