### Biosample collection and processing

Fourteen millilitres of blood will be collected in serum tubes at baseline, midtreatment, end-of-treatment and follow-up visits for analysis of inflammatory cytokines, C reactive protein and immunoglobulins. Tubes will be centrifuged at 2000 RPM (600G) for 15 min following 15 min clotting time for extraction of serum. Aliquots will be stored at −80°C for subsequent batch analysis using ELISA and electrochemiluminescence assays.

At baseline, end of treatment and follow-up visits, an additional 27 mL of blood will be collected in lithium heparin tubes for separation of peripheral blood mononuclear cells (PBMCs) for immunophenotyping. A concurrent full blood count (FBC) will be performed from an EDTA sample (2.6 mL).

CSF will be collected via lumbar puncture before the baseline visit and at the treatment endpoint. This is an optional component of the study in order to ensure that its inclusion does not limit recruitment. CSF will be spun at 400G for 10 min for extraction of immune cells for contemporaneous immunophenotyping alongside PBMC analysis. Supernatants will be stored at −80°C for later batch analysis of relevant immune and protein markers. Immunophenotyping will be performed for subsets of T cells, B cells and monocytes using flow cytometry, run within 24 hours of sample collection.

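### The exploratory safety outcome ends with the 12-month treatment period, with no lag after the last dose, although adverse events are reviewed to Day 547

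*Protocol article*

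**What the plan says.** The Outcome measures section names one primary outcome and then lists further ones, introduced by "Other outcome measures are exploratory and include". One of these is the only adverse event outcome in the article: "The safety and tolerability of azathioprine assessed by the number of adverse events (AEs) recorded during the 12-month treatment period".

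The abstract describes treatment "for 12 months, with a further 6-month follow-up". Table 1 has a row "Adverse events review" that is ticked in every visit column. Two of those visits follow the end-of-treatment visit (Day 365±14): the second imaging visit (Day 410±45) and the follow-up visit (Day 547±14). Safety monitoring bloods are ticked at follow-up, and the table's footnote on monitoring visits ends its list with "day 252 and day 547 (as part of the routine follow-up visit".

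The same outcome list follows immune measures beyond treatment, for example "Change in serum immunoglobulin levels at 6, 12 and 18 months", and has total lymphocyte count at the same three time points. Nothing in the article extends the adverse event outcome past the treatment period or adds a lag after the last dose.

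**The concern.** Azathioprine is described in the Introduction as acting through reduced lymphocyte proliferation. The protocol treats immune effects after stopping as an open question, since it measures lymphocyte count and immunoglobulins six months after treatment ends and repeats blood count, renal and liver tests at that visit. A harm of the same kind that first appears shortly after the last dose, such as an infection or a cytopenia, is then relevant to the drug's safety. As worded, the outcome would not count it in a participant who completed the 12 months.

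This is a stated window, not a detail left for another document. At stake is whether the declared safety result covers a period for which the trial already plans to hold data. With 60 participants randomised 1:1, about 30 per arm, a few events could matter to how the safety result is read.

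**Working it through.** The article gives no figure of its own for this window, so there is none to reproduce. The check is arithmetic on the Table 1 visit days.

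**Inputs (Table 1)**
- End-of-treatment visit: Day 365±14, so Day 351 to Day 379.
- Follow-up visit, the last scheduled adverse event review: Day 547±14, so Day 533 to Day 561.
- Assumptions: treatment starts at Day 0, and a participant who completes the course takes the last dose at about the end-of-treatment visit.

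**Days of collection outside the outcome**

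Uncounted days = follow-up day − end-of-treatment day. Share = uncounted days ÷ follow-up day.

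| Case | Uncounted days | Share of post-baseline days |
|---|---|---|
| Nominal | 547 − 365 = 182 | 182/547 = 33% |
| Shortest gap | 533 − 379 = 154 | 154/533 = 29% |
| Longest gap | 561 − 351 = 210 | 210/561 = 37% |

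The nominal gap agrees with the six-month follow-up in the abstract.

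**From days to events**

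A share of days is not a share of events. If the adverse event rate after treatment is r times the rate on treatment, the share of post-baseline events outside the outcome is 182r ÷ (365 + 182r).
- r = 1: 182/547 = 33%.
- r = 0.5: 91/(365 + 91) = 91/456 = 20%.

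The documents do not give r, so these two values only illustrate the range. They cover adverse events of any cause in both arms together and say nothing about the difference between arms.

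**What does not change**

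The sample size section concerns the gait/axial score only. Widening the adverse event window alters neither the 60 participants nor the stated power.

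**The case against.** The strongest reply is that nothing here is inconsistent. Trials commonly collect adverse events more widely than any single outcome counts them. Table 1 also ticks the review at screening and at the visits before baseline, before any drug is given, so that row was never meant to define the outcome. An on-treatment window is a common choice for drug safety. The outcome is exploratory, the list is not exhaustive, the events are still collected, and the safety board sees interim safety data. A fuller protocol or analysis plan may tabulate later events. Laboratory changes that persist to 18 months are partly covered by the lymphocyte and immunoglobulin outcomes and the Day 547 bloods.

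Most of this stands. It shows that the window is a choice, not a contradiction, and that the data are not lost. It does not supply a lag after the last dose. The 18-month laboratory outcomes would not capture an infection, or a cytopenia that had recovered by Day 547. Tables elsewhere would sit outside the safety outcome as declared here.

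Several stronger readings are tempting, and the document does not support them:
- **Every event after stopping is lost.** The window reads as a 12-month period, and participants withdrawn from treatment are encouraged to keep attending. Events after an early stop but within 12 months can count.
- **Azathioprine would look safer than it is.** No figure in the article gives the rate or the arm balance of later events. If they were mainly background illness in both arms, counting them could dilute a difference.
- **Harm is followed for less time than benefit.** The primary efficacy outcome also stops at 12 months, and the 18-month measures are exploratory.
- **Complications of the second PET scan and lumbar puncture are the main loss.** Both procedures are optional, and their complications bear on the procedures more than on azathioprine.

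**Conclusion.** The point holds as a modest one about drug safety soon after dosing ends. For a participant who completes treatment, the stated outcome stops with the 12-month period and allows no lag, while adverse event review continues to Day 547. Nominally 182 of 547 post-baseline days (33%, or 29% to 37% across the visit windows) lie outside it. This rests on the Table 1 days and on a last dose at about the end-of-treatment visit.

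The number of events involved, and the direction and size of any effect on the comparison between arms, cannot be determined from the article. A reader might infer from the 33% that a third of azathioprine-related harm is hidden. That does not follow, because the figure is calendar time and the concern is greatest for the days just after the last dose. The primary analysis, the sample size and participant monitoring are unaffected.

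**What to change.** Keep the on-treatment count. Extend the safety outcome to adverse events from first dose to the Day 547 visit, and report it by arm in two periods: on treatment (first to last dose), and after the last dose to Day 547. For participants who stop early, the second period begins at their own last dose; a count over the original 12 months can still be derived from the same records.

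The cost is a change to the outcome wording and one extra table, with no new visits, tests or data. The downside is that later events include more background illness, and the two-period split keeps these apart from the on-treatment result.
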